**Manager measures**								
Demographics			x					
Mental health management experience			x					
RTW management experience			x				x	
Work adjustments				x*	x*	x*	x*	
Work demands			x				x	
Autonomy			x				x	
Confidence managing sick leave and RTW			x	x	x	x	x	
RTW competency				x*	x*	x*	x*	
RTW competency (post- RTW)				x**	x**	x**	x**	

Key: x** = measures administered until employee returns to work; x* = measures administered once employee has returned to work; 1 month = measures administered at 1-month follow-up

### Trial feasibility and process-related outcome measures

The primary outcome of this pilot trial is to assess the feasibility of the research procedures (including recruitment, data collection, randomisation, acceptability of the intervention, retention and the presence of any adverse events) to inform the planning of a full RCT and test a full process evaluation methodology in advance of a fully powered trial. Specifically:The willingness of organisations, their workers on long-term sick leave and the line managers of those on long-term sick leave to take part in a 30-month study, and retention through follow-up (12 months) with intervention uptake and completion as primary endpoints.The potential for selection bias in control and intervention organisations as measured using participant characteristics at baseline.Intervention delivery, dose and fidelity whilst the worker is on long-term sick leave, and implementation of intervention delivery and adherence after the worker has returned to work.Acceptability of the intervention from different demographic groups (to understand what works for whom in which circumstances)Willingness and readiness of employers and their workers to adopt the proposed intervention in a manualised format (written as an instruction manual) that is flexible enough to meet individual and organisational needs in different settings.

The corresponding criteria for determining the success of the feasibility are outlined in the study outcome and data analysis section. The Integrative Process Evaluation Framework (IPEF) [34] will be used to evaluate the IGLOo study. The IPEF integrates the Reach, Effectiveness, Adoption, Implementation and Maintenance (RE-AIM) framework [35], and the Realist Evaluation theory [36] and has been developed to understand what works for whom in multilevel interventions such as those used in the proposed study. The RE-AIM framework evaluates five implementation outcomes: reach, effectiveness, adoption (e.g. delivery), implementation (intervention fidelity, costs and use) and maintenance (e.g. acceptability). The Realist Evaluation theory guides data generation to answer the question: “What works, for whom, in what respects, to what extent, in what contexts, and how?” Thus, allowing for the differential outcomes of the intervention for specific demographic groups such as gender and Black, Asian and Minority Ethnicity (BAME) to be identified. The IPEF is therefore a comprehensive five-phased framework guiding the collection, evaluation and reporting of process outcome data during the phases of a ‘real-world’ multi-level intervention: pre-intervention, intra-intervention, implementation and follow-up. The data collection methods outlined below capture the process outcome information using IPEF. In Realist evaluation, programme logic is formulated through CMO configurations. Figure 1 provides an overview of these hypothetical CMO configurations at each level of the IGLOo model. These CMO configurations will be empirically tested and refined based on our analyses.

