## Methods/design

### Study design

The study design follows the UK Medical Research Council guidance for complex interventions [26]. This will be a pilot cluster randomised controlled trial of the IGLOo intervention. The study will last 36 months with organisations participating for 30 months. Within each participating organisation, the recruitment of workers on long-term sick leave will take place over 12 months. Workers will be recruited between >14 and <42 days for their long-term sick leave. Key process outcome measures will be collected monthly through regular meetings with each organisation’s study contact (e.g. key HR staff), while research outcome measures will be collected from each worker and line manager participant at baseline, 3, 6, 9 and 12 months. As a cluster RCT, the unit of randomisation will be the organisation, such that some organisations will receive the pilot intervention and others will not, although the collection of the outcome measures will take place in all participating organisations. Figure 2 shows the study flow diagram, and Table 2 indicates the schedule of enrolment, intervention, and outcome measures. The project has been granted ethical approval by the East Midlands Ethical Advisory Committee. The trial was preregistered in the International Standard Randomised Controlled Trial Number (ISRCTN) registry on 06/10/2022.

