### Sample size

We will recruit eight cluster organisations [32] with ≥ 600 hundred workers (to minimise the risk of missing recruitment targets) into the feasibility pilot study (randomised in each arm) to calculate the target sample size for a definitive RCT. There is no formal requirement to conduct sample size calculations for pilot trials [33], but a sample of at least 100 participants is desirable [26]. Our target recruitment is 50 workers in the intervention arm and 50 workers in the control arm. We have no recruitment targets set for managers. Approximately 13 workers from each organisation will need to be recruited to reach our sample size. However, we aim to recruit 30 workers and 30 managers from each organisation to participate in the study to ensure that, even with a high possible level of attrition, 50 cases (workers) per arm are achieved [26, 33].

The target population is workers on long-term sick leave due to mental ill health or for a condition known to be associated with mental ill health [2, 12–14], who will be identified by their workplace between > 14 and < 42 days of their long-term sick leave and sent an invitation on behalf of the research team to participate in the study. The line manager of the individual worker on long-term sick leave will also be invited to participate in the study. Participation of the line manager is entirely voluntary, irrespective of whether their worker is taking part.

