#### Allocation to intervention

In this pilot RCT, organisations will be randomised using a 1:1 ratio. Randomisation to trial conditions (intervention versus control) will be carried out by assigning pre-prepared envelopes containing the allocation outcomes to the organisation. In each participating organisation, participants (i.e. senior leaders, managers and workers) will partake in the condition their organisation is allocated to and will therefore not be blinded in their group allocation. Prior to the intervention being deployed, an organisation-wide survey will take place to explore the ethos, culture and attitudes towards procedures for managing mental health and return to work in the organisation. All workers at the organisation will be eligible to participate in this.

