**Enrolment**								
Organisation recruitment	x							
Eligibility Screen	x							
Organisation informed consent	x							
Allocation		x						
Manager informed consent			x					
Worker informed consent			x					

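### Workers are recruited and measured at baseline after their organisation has been allocated, unblinded; the plan measures the resulting selection risk but states no step to reduce it

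*Protocol article*

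**What the plan says.** **Order of events.** Under Study design, "the unit of randomisation will be the organisation", and within each organisation "the recruitment of workers on long-term sick leave will take place over 12 months". Table 2 gives allocation its own column, ahead of the baseline column in which the row "Worker informed consent" is marked. Under Sample size, workers are "identified by their workplace between > 14 and < 42 days of their long-term sick leave" and are then sent an invitation on the research team's behalf.

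**Blinding.** Under Allocation to intervention, senior leaders, managers and workers take the condition of their organisation and "will therefore not be blinded in their group allocation".

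**What is offered.** Intervention workers get an online toolkit and up to three telephone coaching sessions (Intervention). Control organisations carry on as usual, and their workers complete the same measurements (Active control group). HR, occupational health and leaders receive the Phase 1 e-learning only in the intervention arm. It includes a module on embedding the toolkits and engaging stakeholders.

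**What is checked.** Trial feasibility and process-related outcome measures lists "The potential for selection bias in control and intervention organisations as measured using participant characteristics at baseline". The Statistical analysis plan section adds a comparison of the arms at baseline. The recruitment paragraph under Pre-study/pre-intervention start goes further: numbers eligible and consenting are collected in both arms, and representativeness is judged by setting organisational records against the baseline demographics of consenters.

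**What is at stake.** The Statistical analysis plan section uses the between-group effect size and the ICC to inform the main-trial sample size. It calls the results preliminary.

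**The concern.** In a cluster trial, randomisation balances organisations. It does not protect the comparison of workers who join afterwards. Here the people who identify workers work in an organisation whose arm is known, and the worker's reason to say yes may differ: coaching and a toolkit in one arm, questionnaires alone in the other. If willingness to join is related to how long someone will be off sick, and that selection differs by arm, the arms differ in sick-leave days with no intervention effect. The bias could run in either direction.

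A second route is timing. Sick-leave days are counted from the first day of leave (Primary outcome measures, phases 2 and 3), but workers enter at any point in a window of several weeks. Someone enrolled late has, by definition, not yet returned. If one arm enrols later on average, the difference goes straight into the outcome.

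Baseline self-reports such as PHQ-9 and return-to-work self-efficacy may also be coloured if the worker already knows the arm.

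**Working it through.** **The plan's own figure.** Eight organisations at 1:1 is 4 per arm. 50 / 4 = 12.5, so 13 workers per organisation, as stated. The protocol gives no target effect, alpha or power, so there is no power calculation to reproduce.

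**Scale.** The review cited in the Background gives an SMD of −0.25 and 25 fewer days in a year, which implies an SD of 25 / 0.25 = 100 days. This is a background benchmark only.

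**Bias from differential consent.** Inputs: consent rates p and correlation r between willingness to consent and sick-leave duration. The protocol states neither, so all values are assumptions; 50% and 25% are its own green and red recruitment thresholds (Study outcome and data analysis). Under a normal selection model, the mean shift among consenters is r × λ(p) SD, with λ(p) = φ(z) / p and z the (1 − p) normal quantile.

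- λ(0.50) = 0.798; λ(0.35) = 1.058; λ(0.25) = 1.271.
- Same direction of selection in both arms: bias = r × [λ(p₂) − λ(p₁)], with p₁ the higher consent rate.

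| Consent | Bracket | r = 0.2 | r = 0.3 | r = 0.5 |
|---|---|---|---|---|
| 50% v 50% | 0 | 0 | 0 | 0 |
| 50% v 35% | 0.26 | 0.052 SD | 0.078 SD | 0.130 SD |
| 50% v 25% | 0.47 | 0.095 SD | 0.142 SD | 0.237 SD |

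Against 0.25 SD, the second row is 21% to 52% (0.052 / 0.25 and 0.130 / 0.25). A milder case, 50% v 40% with r from 0.1 to 0.3, gives 7% to 20%.

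Equal consent rates do not by themselves rule bias out. If 50% consent in each arm but only one arm selects on prognosis, the bias is r × 0.798, which is 0.160 SD at r = 0.2.

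**Bias from enrolment timing.** The window runs from day 15 to day 41, a spread of 26 days. Assuming a constant rate of return to work, an arm difference of 5 days in mean enrolment day adds about 5 days to the outcome difference: 5 / 100 = 0.05 SD, or 20% of the 25-day benchmark.

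**Can a baseline comparison show it?** With 50 per arm, design effect = 1 + (12.5 − 1) × ICC and SE = √(2 × design effect / 50). The ICC is assumed.

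| ICC | Design effect | SE (SD units) | Power to show a true 0.25 SD imbalance |
|---|---|---|---|
| 0 | 1.000 | 0.20 | 24% |
| 0.05 | 1.575 | 0.25 | 17% |
| 0.10 | 2.150 | 0.29 | 14% |

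A baseline table would usually miss an imbalance of that size. The same SEs apply to the pilot effect itself, so random error is at least as large as every bias in the consent table except the most extreme one (0.237 SD), which lies inside the SE range.

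**The case against.** The strongest reply is that this is a feasibility pilot. Potential selection bias is one of its listed questions, results are to be read with caution, and no weight goes on p values. That stands and limits the severity. It does not remove the point, because the effect size still goes forward to the main-trial sample size, and a pilot is the natural place to try out recruitment safeguards.

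A reader might infer that the plan looks for selection bias only among those who consented. It does not: the eligible and consenting counts and the comparison with organisational records reach beyond consenters. What can be said is narrower. The records comparison covers demographics, is not stated to be made by arm, and names no prognostic item.

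A reader might also take 0.25 SD as the effect this trial hopes to see. The protocol sets no such target.

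Nor does the article say that invitations disclose the arm, or that employers choose workers by judgement. It says that participants are not blinded and that the workplace does the identifying. Invitation wording may be set out elsewhere, and covariates for the pilot comparison may be left to the analysis plan still to be finalised. The article itself speaks of covariate control for the future trial.

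Finally, the order is partly inherent: new absences are recruited over a year, with study publicity running throughout. Concealing the arm until after baseline will not always succeed.

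**Conclusion.** The concern holds in a limited form. Recruitment, consent and baseline follow a known allocation, what is offered differs by arm, and the plan as published measures the resulting risk without stating a step to reduce it. Enrolment timing is a further and direct route into the outcome.

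The size cannot be known from the protocol. Under assumed correlations of 0.2 to 0.5, it is 0.05 to 0.13 SD at 50% v 35% consent and 0.09 to 0.24 SD at 50% v 25%. It is zero if selection is equal in both arms. It would be wrong to conclude that the pilot estimate is biased by a known or necessarily large amount. Sampling error is of similar size or larger, but a larger trial recruited in the same order would shrink that error and leave the bias. Whether the main trial would keep this order is not stated. The change is worth making because it is cheap.

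**What to change.** 1. Use one arm-neutral invitation and information text. Where feasible, take the worker's consent and baseline questionnaire before the condition is disclosed.
2. Have employers invite every eligible absence that reaches the window, by a fixed rule.
3. Adjust the pilot comparison of sick-leave days for days already absent at consent. As a sensitivity analysis, adjust also for baseline PHQ-9 and return-to-work self-efficacy. All three are already collected. The two self-reports belong in a sensitivity analysis because they may be affected if the arm is known.
4. Make the planned eligible-versus-consenting comparison by arm, and add day of leave at invitation and reason for absence where records give them.

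**Cost.** Items 1 and 2 need reworded invitations, an ethics amendment and a short instruction to employers. Item 3 needs no new data, and item 4 only what records already hold. Some workers may still learn the arm from workplace communications, so the bias would be reduced, not excluded.

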#### Pre-study/pre-intervention start

Study reach will be assessed by collecting data on the number of organisations approached to participate in the study, number of expressions of interest and the number that consent to participate. Methods used to recruit these organisations will be documented and included in the evaluation to understand the underlying motivation of the organisation’s key stakeholders for participating in the study [37]. From the consenting organisations, we will collect long-term sickness absence data for the past 12 months (only total numbers and % by reasons), size of organisation and sector. We will also collect information from lead stakeholders (e.g. director of human resources) on their ‘readiness’ and expectations for the intervention. These data will help us identify potential *Context*ual barriers and facilitators to implementing the intervention.

Omnibus contextual factors (i.e. factors within the study which may inhibit or facilitate the extent to which the study is implemented) will be examined at the start of the study by collating views of the workforce through an organisational-wide online survey on workers’ knowledge of policies and practices around long-term sickness absence management and return to work support, perceptions of leaders commitment to supporting mental health and their communications for mental health support within the workplace [38]. This information will be used to examine leaders’ commitment to, and transparency of their commitment towards mental health conditions [39]. The survey will be sent out to control and intervention organisations at the start of the study. Discrete contextual factors (i.e. specific situational conditions that impact implementation) will be identified if and when they emerge throughout the pilot [40]. At the time of writing, there is upcoming industrial action in the UK in some of the sectors and we expect this, as well as other confounding social and economic factors, to influence participants’ experiences of the IGLOo intervention. We will therefore include questions about arising circumstances which may inhibit or facilitate implementation in the qualitative interviews with participants.

*Recruitment for phases 1 and 2*: information on the number of eligible staff for phase 1 (e.g. senior management team, HR staff) and the number consenting to take part will be collected in the intervention organisations only. For *phase 2* (workers on long-term sick leave and their managers), the number eligible to take part and the number consenting will be collected in both the control and intervention organisations. Reach will be assessed by comparing the overall eligible participant population invited to take part (the number of workers on long-term sick leave eligible for phase 2), with those who consent to participate (recruitment and reach are not assessed for phase 3 as all phase 2 participants automatically enter phase 3). Representativeness of the participant population will be assessed from information obtained through organisational records and will be compared against demographic information from the baseline questionnaires of consenting workers.

#### Intra-intervention and implementation

Guided by the IPEF, we will assess the implementation of intervention activities evaluation for each intervention phase. Intervention dose and compliance will be assessed through analytics data, including number accessing online e-learning or toolkits, number of downloads of resources, completion of modules or steps and downloads of self-guide exercises. Acceptability and usability of the intervention will be assessed using questionnaires and interviews at the end of each intervention phase. The number of coaching sessions attended by phase 2/3 worker participants will be documented, and a random selection of coaching session will be audio-recorded to assess fidelity. We will ask participants to send us screenshot/copies of completed learning activities, checklists, goal-setting and action-planning sheets and other record sheets.

Structured interviews will be conducted with all participants at the end of each intervention phase with a view to explore the mechanisms by which the intervention works. For example, we will explore how participants have attempted to transfer knowledge, skills and methods learned from each intervention phase within their respective roles (e.g. as a leader implementing policies, as a line manager supporting a worker on sick leave, and as a worker requesting work adjustments). Questionnaires and interviews will also be used to understand intentions and motivations for intervention engagement, changes to cognitions and behaviours as a result of the intervention, and any contextual factors (barriers and facilitators) that may have influenced engagement with the intervention materials.

#### End of study

At the end of the 30-month study participation, we will interview control and intervention employers (e.g. human resources/senior managers) to explore their perceptions of the study including data collection methods and time commitments. To evaluate maintenance, we will also explore interest in on-going usage of the intervention materials and whether the intervention could form part of their return-to-work policies and processes moving forward. Finally, we will re-examine the omnibus contextual factors in control and intervention organisations by repeating organisational-wide online survey.

### Main trial research-related outcomes

We will collect the following data to inform the feasibility of the pilot study as a whole.

#### Phase 1 measures

For phase 1 participants, the outcome data will be collected using questionnaires at baseline (pre-intervention) and post-intervention approximately 1–2 months after being given access to the e-learning resources. Information collected at baseline will include questions about awareness of current policies and procedures, job autonomy, job demands (Health and Safety Executive Job Demands Scale) [41], demographic information including occupational classification (Standard Occupational Classification, 2020) [42] intervention readiness and communication about mental health and resources. The latter two questionnaires will be asked again at 1-month follow-up.

#### Primary outcome measures (phases 2 and 3)

The primary research outcome of the study, the total number of days on sick leave, will be collected for control and intervention participants. The number of sick leave days will be calculated from the first day of sick leave recorded on a participant’s ‘fit note’ (obtained from their general practitioner or medical doctor and submitted to their employer), until their first day back at work using self-report data from the participant. Sick leave days are counted in calendar days and not just the days a person typically works on. For example, weekends and non-working days are counted as part of sick days. The information will be collected from participants via text messaging at monthly intervals as well as asked in the baseline questionnaire, and in their 3-, 6-, 9- and 12-month follow-up questionnaires. Participants will be asked whether they have returned to work and, if so, what was the date of their first day back at work. If they have not returned to work during their participation, then the last point this question will be asked will be at their final data collection point at 12 months (see Table 2). Self-report of sickness absence has been shown to be adequately reliable when compared with organisational records [43, 44].

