An interplay of factors beyond the health condition is known to impact both return-to-work (RTW) outcomes (defined as the number of sick leave days until the first day of RTW with adjusted working hours or usual working hours) [15] and sustainable RTW outcomes (defined as number of days staying in work over a 6-month period after returning with no exit or long-term sick leave re-occurrence) [16]. Lower education and socio-economic status, older age, lower self-efficacy, poor line manager and/or co-worker support, inadequate work adjustments or lack of freedom to work flexibly (i.e. job crafting) and inadequate workplace return-to-work policies can all hamper sustainable return to work [16–19]. This has a detrimental impact on workers, leading to early retirement, job termination, unemployment [4] and reduced quality of life [9]. It also has a negative impact on employers through sick pay, staff turnover and productivity loss [9] and, more broadly, on society through health-related state benefits.

Evidence suggests that return-to-work outcomes in those with poor mental health are enhanced when symptom/problem-focused interventions (e.g. work-focused Cognitive Behavioural Therapy or solution-focused skills training ) are combined with elements of their workplace (e.g. contact with line manager during absence) [15, 16, 19]. A Cochrane review into mental health and long-term sick leave [19] found moderate evidence that a combination of work-directed and clinical interventions (such as psychological treatment) reduces sickness absence days within the first year of follow-up (SMD −0.25, 95% CI −0.38 to −0.12: 9 studies). Whilst this translates “to 0.5 fewer (95% CI −0.7 to −0.2) sick leave days in the past 2 weeks or 25 fewer days during 1 year (95% CI −37.5 to 11.8)” [19], the authors of the review propose that the integration of clinical and work-directed elements of an intervention is key to improving work outcomes.

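### Sick days are counted from before enrolment and workers are identified after unblinded allocation, so any difference in entry day between arms or organisations would pass into the effect size and ICC

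*Protocol article*

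**What the plan says.** All references are to the protocol article.

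- **Clock.** Under Primary outcome measures (phases 2 and 3), "The number of sick leave days will be calculated from the first day of sick leave recorded on a" participant's fit note, "until their first day back at work using self-report data from the participant". For those who have not returned, "the last point this question will be asked will be at their final data collection point at 12 months".
- **Entry.** Study design: "Workers will be recruited between >14 and <42 days for their long-term sick leave". Sample size describes the target population as workers "who will be identified by their workplace between > 14 and < 42 days of their long-term sick leave and sent an invitation".
- **Allocation.** Study design: "the unit of randomisation will be the organisation". Table 2 marks worker consent in the Baseline column, after the Allocation column. Allocation to intervention says that senior leaders, managers and workers are not blinded.
- **Phase 1.** Under Intervention, HR, occupational health and others who manage absence in intervention organisations receive e-learning. Active control group says that control organisations receive no training.
- **Analysis.** The Statistical analysis plan section compares total calendar sick days between arms. It uses the between-group effect size and the ICC from a mixed model to inform the main-trial sample size. The Cox model planned for that trial is described with censoring; delayed entry is not mentioned.

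**The concern.** A worker enrolled on day *e* of absence cannot have returned before day *e*. Anyone who went back sooner is not in the data. Later enrolment therefore selects longer absences and raises the mean total, even if the intervention does nothing. The maximum count also moves with entry day, because follow-up runs 12 months from baseline.

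This does no harm to the comparison if entry day has the same distribution in both arms. The design does not secure that. Staff who know the allocation find the workers, and in one arm the people who run absence management have been trained. With about four organisations per arm, local differences in how quickly cases are picked up may also fail to balance. A gap between arms would distort the effect size, and variation between organisations within an arm would add to the ICC. Both numbers are meant to be carried into the definitive trial.

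**Working it through.** **The plan's own figures.** 100 workers / 8 organisations = 12.5, rounded up to 13, as the Sample size section states. At 1:1, eight organisations give 4 per arm. The article gives no figure for the bias examined here.

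**Inputs from the article.** In whole days, the window of more than 14 and fewer than 42 is day 15 to day 41, a width of 41 − 15 = 26 days. With 365 days of follow-up from baseline, the maximum count runs from 15 + 365 = 380 to 41 + 365 = 406 days.

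**Assumptions.** Absence duration *T* follows the same Weibull law in both arms (no true effect), with mean 60 to 180 days and shape 0.7 (falling return rate), 1.0 (constant) or 1.5 (rising). All workers in an arm enter on the same day *e*. None of these values comes from the article.

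**Formula.** With survival function S, the expected total count for entry on day *e* is

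m(e) = e + ∫ from e to e+365 of S(t)/S(e) dt.

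The spurious difference is m(later) − m(earlier).

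| Entry gap (days) | Falling rate | Constant rate | Rising rate |
|---|---|---|---|
| 5 (day 25 v 30) | 6.9 to 7.3 | 5.0 | 2.5 to 3.3 |
| 10 (day 20 v 30) | 14.1 to 14.8 | 10.0 | 4.8 to 6.5 |
| 15 (day 20 v 35) | 20.9 to 21.8 | 15.0 | 7.5 to 10.0 |
| 26 (day 15 v 41) | 36.3 to 37.9 | 26.0 | 13.0 to 17.2 |

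The bias depends on some workers returning inside the window. In these scenarios, 7% to 37% of those absent at day 15 are back by day 41. If nobody returned in that interval, entry day would not change the true total.

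**Counting from enrolment instead.** Subtracting the gap from each cell shows what would remain. It is 0 under a constant rate, about +2 to +12 days under a falling rate, and about −2 to −13 days under a rising rate. A change of origin alone is therefore not a general remedy.

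**Adjusting for days already absent.** Within each shape the bias is close to proportional to the gap. For example, with shape 0.7 and mean 60, 6.9/5 = 1.38, 14.1/10 = 1.41 and 36.3/26 = 1.40. A linear covariate whose slope is estimated from the data can absorb this; a slope fixed at 1 cannot.

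**Cox model, no true effect.** This was simulated with 3,000 per arm and exponential remaining absence of mean 90 or 120 days. Hazard ratios above 1 mean faster return in the earlier-entering arm.

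| Entry days | Clock from day 1, no delayed entry | Clock from day 1, delayed entry |
|---|---|---|
| 20 v 30 | 1.10 to 1.13 | 1.01 |
| 15 v 41 | 1.24 to 1.30 | 0.99 to 1.00 |

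**How large could a chance gap be?** If organisation mean entry days have standard deviation *s*, the gap between arms has standard deviation s × √(1/4 + 1/4) = 0.71s, leaving aside sampling within organisations. A one-standard-deviation gap of 5 days needs s of about 5/0.71 = 7 days; a gap of 10 days needs about 14. The article gives no information on *s*.

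**The case against.** The strongest case against has five parts.

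1. **Pilot status.** The primary outcome is feasibility, and none of the four traffic-light criteria uses sick days. Results are to be treated as preliminary. Under an exponential remaining absence with median 120 days (assumed), capped at 365, the standard deviation is about 119 days. With 50 per arm the standard error is 119 × √(2/50) ≈ 24 days before clustering, so a 10-day bias lies well inside the noise. This stands and limits the severity. It does not dispose of the point, because the same outcome definition and model are intended for the definitive trial, where a bias would not shrink with sample size.
2. **Left to the SAP.** A separate analysis plan is promised and may already handle this. That is possible. But the outcome, its origin and the contrast are fixed in the article, and as stated they give a biased answer whenever entry timing differs.
3. **Existing safeguards.** Selection bias is a named feasibility outcome, numbers eligible and consenting are recorded in both arms, baseline characteristics are compared, and days off sick are recorded at baseline. These would help to reveal an imbalance; none is stated to remove it from the comparison.
4. **No gap is predicted.** The Phase 1 modules do not mention invitation timing, the same window applies in both arms, and monthly meetings are held with every organisation. This stands: the point is conditional.
5. **The outcome matches the Background definition of return to work.** This also stands, and is a reason to keep total days as a descriptive measure.

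A reader might go further and infer that the trial will show a false benefit of 13 or 26 days, as large as the published one. The documents do not support that. A constant-rate model simply returns whatever gap is put in, and 26 days needs every worker in one arm to enter on day 15 and every worker in the other on day 41. The yardstick is weak too: the Background gives "or 25 fewer days during 1 year", but the 0.5 days per 2 weeks it equates with this comes to 0.5 × 26 = 13 days a year.

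**Conclusion.** The point holds as a conditional weakness of moderate severity. The outcome clock starts 15 to 41 days before entry, entry follows unblinded allocation and is controlled by the employer, and the stated comparison does not account for time already absent. With no true effect, a 10-day gap in entry day would appear as roughly 5 to 15 sick days, and a 5-day gap as roughly 2.5 to 7. These figures rest on assumed Weibull durations and on a gap that the protocol neither predicts nor rules out. The Discussion remark that people absent for 6 months seldom return hints at a falling rate, and so at the upper part of each range, but does not establish it.

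Two further inferences should be resisted. The stop-go decision is not at risk from this. And the arms are not shown to be selected differently: early returners are lost from both, and only a difference in timing makes that loss unequal.

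**What to change.** - Keep total calendar days from the first day of absence as the descriptive outcome.
- Make the between-arm comparison with a time-to-return model that has delayed entry at the enrolment day, or include days already absent at baseline as a covariate in the pilot mixed model from which the effect size and ICC are taken.
- State delayed entry for the main-trial Cox model.
- Do not rely on counting from baseline alone. It is equivalent to delayed entry only under a constant return rate, so use it only together with adjustment for days already absent.
- Report entry day by arm and by organisation as a feasibility result. Say whether the window applies to identification or to consent, since Study design and Sample size word this differently and consent could fall after day 41.

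The cost is wording in the analysis plan and outcome definition. The fit-note start date and days off sick at baseline are already collected. Delayed entry assumes that, among workers still absent, entry day carries no further information about return. It does not correct selection on other characteristics, for which the planned baseline comparisons remain necessary.
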